### 2.8. Oversight and Monitoring

Because this study involves a minimal-risk, non-pharmacological behavioral intervention that does not alter standard clinical care or expose participants to additional medical procedures, a formal independent Data Monitoring Committee (DMC) is not required. No investigational products, device interventions, or invasive procedures are involved, and all participants receive standard clinical management irrespective of trial allocation.

Adverse events related to exercise testing or rehabilitation, including but not limited to exercise-induced syncope, clinically significant arrhythmia, or other unexpected medical events, will be captured through the electronic medical record system during follow-up visits. Such events will be identified and reported by the attending rehabilitation physician responsible for conducting the cardiopulmonary exercise testing or supervising rehabilitation sessions. The principal investigator will review all safety data at monthly intervals. Any serious adverse events will be reported to the IRB of TCVGH within 24 h of identification.

Study oversight is performed by the principal investigator and the institutional research office at TCVGH, which ensures compliance with ethical standards and trial governance requirements. No interim analyses or stopping guidelines are planned, as the intervention is informational in nature and does not introduce clinical risk. Trial monitoring focuses on data accuracy and timely reporting of any unexpected issues. Research staff will review screening logs, enrollment flow, and data quality at regular intervals, and any concerns will be documented and addressed according to institutional procedures. Given the low-risk profile and the absence of safety-related endpoints, no external monitoring body is deemed necessary.

No interim analyses or formal stopping guidelines are planned, as the intervention is informational in nature and does not introduce additional clinical risk. Trial monitoring focuses on data completeness, accuracy, and protocol adherence. Research staff will conduct regular internal reviews of screening logs, enrollment flow, and data quality, and any protocol deviations or unexpected issues will be documented and managed according to institutional procedures. Given the low-risk profile of the study and the absence of safety-related endpoints, no external monitoring body is considered necessary.

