## Abstract

**Background**: Despite clear evidence supporting the benefits of outpatient cardiac rehabilitation for acute coronary syndrome survivors, participation rates remain low. Many patients face person-level and system-level barriers for outpatient rehabilitation, and their motivation often wanes soon after discharge. Cardiopulmonary exercise testing provides individualized physiological information and may act as an external cue that enhances engagement, yet no randomized trial has evaluated whether announcing a scheduled test can influence rehabilitation attendance. **Methods**: This single-center, parallel-group, single-blind randomized controlled trial investigates whether informing patients during hospitalization that a cardiopulmonary exercise test will be conducted at their first rehabilitation visit increases early outpatient attendance. Patients with acute coronary syndrome are randomized 1:1 to receive either standard discharge education or the same education plus an exercise testing announcement. All other clinical care follows routine practice. The primary endpoint is completion of the first rehabilitation clinic visit within 30 days. Secondary outcomes include attending at least six rehabilitation sessions within 12 weeks, actual exercise testing completion, and any safety events. The analyses will follow the intention-to-treat principle and will use logistic regression and time-to-event models. The planned sample size is 200 participants.

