### 2.3. Interventions

All participants will receive standardized in-hospital education delivered by trained staff. The education covers the goals and components of cardiac rehabilitation, the benefits of regular physical activity, basic home exercise recommendations, medication adherence, and risk factor management. Before discharge, the research team will schedule a first visit at the rehabilitation clinic within approximately 30 days after discharge for all enrolled patients, and this appointment will be documented in the discharge summary. The selection of attendance within 30 days of hospital discharge is based on evidence that earlier scheduling within the first few weeks is associated with higher initial participation, while scheduling beyond one month is linked to lower uptake [40,41].

Patients in the CPET announcement group (intervention arm) will receive the standard education supplemented by a specific behavioral strategy. The research team will formally announce that a CPET would be arranged at their first rehabilitation outpatient visit. The educator uses a standardized script to emphasize that CPET would assess their current cardiopulmonary fitness, compare it with age-matched norms, and guide the intensity of subsequent exercise training. Patients are given a one-page leaflet describing the CPET procedure, safety measures, and clinical benefits in simple language. The discharge instructions explicitly note “rehabilitation clinic visit and cardiopulmonary exercise testing” to reinforce the expectation.

In the standard care group (control arm), patients will receive the same standard education and pre-scheduled rehabilitation clinic appointment, but CPET will not be proactively mentioned during hospitalization.

Ethically, the intervention is defined strictly as the “pre-discharge declaration” and the provision of informational materials. Access to clinical services remains equitable; physicians in both arms retain full discretion to order CPET based on clinical indications post-discharge.

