### 2.5. Outcome and Covariates

The primary outcome is their attendance at the rehabilitation clinic within 30 days of hospital discharge. Attendance is defined as completion of at least one scheduled rehabilitation outpatient visit during this period at TCVGH. Attendance is verified via the hospital’s electric medical record system. Given the study’s focus on institutional workflow integration, visits to external facilities are not counted toward the primary endpoint to maintain data consistency.

Secondary outcomes include the following:Cardiac rehabilitation program participation: completion of a predefined early rehabilitation course within 12 weeks after discharge, defined as attending at least six supervised rehabilitation sessions.CPET completion: whether a CPET is ultimately performed during follow-up, irrespective of group.Safety: occurrence of adverse events potentially related to exercise or rehabilitation during the observation period, such as syncope during exercise sessions, sustained arrhythmias requiring urgent management, or emergency department visits or rehospitalization that related to therapeutic exercise

We will also collect the following covariates and potential determinants:Demographic factors—age, sex, body mass index (BMI).Socioeconomic and lifestyle factors—education level, employment and physical workload, physical activity level prior to ACS, and current smoking status.Social context—residential distance from the hospital and whether a family member accompanied the patient during hospitalization.Comorbidities—hypertension, diabetes mellitus, dyslipidemia, and renal impairment.ACS characteristics—ACS type based on electrocardiographic (ECG) findings (STEMI or NSTEMI), peak creatine kinase (CK) level, left ventricular ejection fraction (LVEF) by ECG, and hospitalization LoS.

In addition, to assess key behavioral constructs referenced in the theoretical framework, cardiac self-efficacy will be measured at baseline using the validated Cardiac Self-Efficacy Scale (CSES). The CSES is a disease-specific instrument designed to evaluate patients’ confidence in managing symptoms, maintaining physical function, and engaging in recommended health behaviors following cardiac events [42]. The questionnaire will be administered at the time of hospital discharge, prior to randomization. Higher scores indicate greater perceived self-efficacy related to cardiac disease management.

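### Safety is a secondary outcome, yet Section 2.8 says there are no safety endpoints and describes no attendance-independent way of finding exercise-related emergency visits and readmissions

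*Protocol article*

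**What the plan says.** Section 2.5 (Outcome and Covariates) lists among the secondary outcomes "Safety: occurrence of adverse events potentially related to exercise or rehabilitation during the observation period". Its examples include syncope and sustained arrhythmia, and also "emergency department visits or rehospitalization that related to therapeutic exercise". The abstract agrees: "Secondary outcomes include attending at least six rehabilitation sessions within 12 weeks, actual exercise testing completion, and any safety events".

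Section 2.8 (Oversight and Monitoring) says otherwise: "Given the low-risk profile and the absence of safety-related endpoints, no external monitoring body is deemed necessary". The paragraph after it repeats the statement almost word for word. On capture, Section 2.8 says that adverse events "will be captured through the electronic medical record system during follow-up visits" and are to be "identified and reported by the attending rehabilitation physician responsible for conducting the cardiopulmonary exercise testing or supervising rehabilitation sessions". It names no other reporter and describes no search of the records.

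Section 2.8 also says that the intervention "does not alter standard clinical care or expose participants to additional medical procedures". In Section 2.3 (Interventions) the research team is to "formally announce that a CPET would be arranged at their first rehabilitation outpatient visit". Section 2.3 further defines the intervention as the announcement and its written material alone, and leaves physicians free to order CPET in either arm. It gives advice on exercising at home to all participants.

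**The concern.** There are two separate problems.

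The first is a contradiction. A listed secondary outcome cannot also be absent, and the absence is used as a reason in the oversight rationale.

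The second is ascertainment. The only reporter named is a physician whom a patient meets by coming to rehabilitation. Coming to rehabilitation is the behaviour that the intervention is meant to change. Where an event can happen to any randomized patient but is found mainly in those who attend, the arms are searched with different intensity. Recorded counts could then differ with no difference in risk, and events in non-attenders would go unrecorded. The expedited report of serious events to the ethics board shares the gap, because its clock starts at identification.

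The primary outcome is not affected.

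**Working it through.** **Inputs.** Section 2.6 plans 25% attendance with the announcement, a gain of 15 percentage points, so 10% without it (the cited background rate is below 10%). Two-sided alpha is 0.05, power is 80%, and about 100 patients per group are required.

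**The plan's own figure.** With pooled variance under the null and mean proportion 0.175:

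n = [1.960 × √(2 × 0.175 × 0.825) + 0.842 × √(0.10 × 0.90 + 0.25 × 0.75)]² / 0.15² ≈ (1.053 + 0.443)² / 0.0225 ≈ 99.5, that is 100 per arm.

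The stated figure reproduces. The planning rates are used below only to illustrate ascertainment. The article gives no figure for the safety outcome.

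**Which events are at issue.**
- *Events at a CPET or a supervised session.* A patient who attends nothing cannot have one, and the supervising physician is the natural observer. If attendance is 2.5 times as high and risk per attender is equal, such events really are 2.5 times as frequent per randomized patient. That is an effect of exposure, correctly recorded, and not bias.
- *Emergency visits and readmissions related to exercise.* These happen outside the clinic and can follow exercise at home, which both arms are advised to do. No route to them is described for a patient who does not attend. Only this component is at issue.

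**Size for that component.** Assume that true risk is equal in both arms and does not depend on attendance, that every event in an attender is recorded, and that a share q of events in non-attenders is recorded. The recorded share of true events is then a + (1 − a)q, where a is attendance. The spurious ratio, intervention to control, is

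(0.25 + 0.75q) / (0.10 + 0.90q).

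The counts assume, for illustration, a true risk of 5% and 100 patients per arm. That gives 5 true events per arm, so the recorded count is 5 × the recorded share.

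| q (assumed) | Recorded share, control | Recorded share, intervention | Spurious ratio | Recorded events, control v intervention |
|---|---|---|---|---|
| 0 | 0.100 | 0.250 | 2.50 | 0.50 v 1.25 |
| 0.10 | 0.190 | 0.325 | 1.71 | 0.95 v 1.63 |
| 0.25 | 0.325 | 0.4375 | 1.35 | 1.63 v 2.19 |
| 0.50 | 0.550 | 0.625 | 1.14 | 2.75 v 3.13 |
| 1 | 1.000 | 1.000 | 1.00 | 5.00 v 5.00 |

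With q = 0 and assumed true risks of 2% to 10%, recorded events run from 0.2 v 0.5 (100 × 0.02 × 0.10 and × 0.25) to 1.0 v 2.5 (100 × 0.10 × 0.10 and × 0.25).

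**The contradictions.** Section 2.5 and the abstract list safety as an outcome, and Section 2.8 says twice that there is none. Both cannot stand. The statement on additional procedures is in tension with the announced CPET rather than flatly contradicted by it. It is literally consistent with defining the intervention as the announcement alone, but more CPETs in the announced arm are foreseeable, and Section 2.5 counts CPET completion as an outcome.

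**The case against.** Five fair points can be made for the plan.

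- *Follow-up visits need not mean rehabilitation visits.* Section 2.2 requires planned cardiology outpatient follow-up at the same hospital, so non-attenders should also leave in-house records. This stands. A reader might infer that events are captured only at rehabilitation visits, but the text does not say so. It does name only the rehabilitation physician as reporter, and it does not say that anyone searches cardiology, emergency or admission records for this outcome.
- *A 2.5-fold excess is not a measure of bias.* This stands. For test and session events it would be a true exposure effect. For emergency visits and readmissions it is the extreme case, in which nothing is recorded in non-attenders.
- *The planning rates do not show who goes unobserved.* A reader might infer that 75% to 90% of patients (1 − 0.25 and 1 − 0.10) are never observed. The documents do not support this. The rates concern a first visit within 30 days, whereas program participation is followed to 12 weeks, and cardiology visits are left out.
- *No between-arm safety test is specified, and events will be few.* This is true and limits the consequence. The outcome will still be reported under an intention-to-treat heading, and a handful of unevenly found events is easily misread.
- *A journal article leaves detail to the full protocol.* That would answer a complaint about missing detail. Here the article states a capture rule and a reporter, and the rule as written falls short for one named component of the outcome.

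**Conclusion.** The concern holds in a limited form. The contradiction between Section 2.8 and both Section 2.5 and the abstract is certain. Followed as written, the capture rule makes detection of exercise-related emergency visits and readmissions depend on attendance. It does not do so for test and session events.

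The documents do not fix the size. The spurious ratio lies between 1.0 and 2.5, with 1.14 and 1.35 at assumed capture of 50% and 25% in non-attenders. The range rests on the planning attendance rates standing for contact with the rehabilitation team, on equal true risk, and on complete capture in attenders. Expected counts are a few events per arm at most under the assumed risks.

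Two stronger inferences should be resisted. The false statement about endpoints does not itself bias anything, because any bias comes from the capture route. It also does not follow that an external monitoring body is needed, only that one stated reason for having none is wrong. The change should be made, but it concerns a secondary outcome.

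**What to change.** 1. Identify emergency visits and readmissions at the study hospital by the same record query for every randomized patient, from discharge to 12 weeks, whether or not the patient attended. Twelve weeks matches the participation outcome in Section 2.5.
2. Have relatedness to exercise judged blind to arm. Section 2.4 accepts that outpatient clinicians cannot be fully blinded, so the treating physician's judgement alone is not enough.
3. Report these events by arm per randomized patient. Report CPET and session events in the same way, and also per test and per session performed, so that exposure and risk can be told apart.
4. State that events at other hospitals are not seen.
5. Remove or correct the claim of no safety endpoints in both places in Section 2.8, and restate the oversight rationale without it.
6. Reconcile the statement on additional procedures with the announced CPET, using Section 2.3's definition of the intervention as the announcement alone and acknowledging that CPET use may differ between arms.

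The cost is one further query of a record system already used to verify the primary outcome, a blinded review of what is probably a small number of events, and corrected text. Recruitment is described as ongoing, so the change can still be made before analysis. Because the query works from records, it can cover patients already enrolled.

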### 2.9. Confidentiality

All participant information will be collected, stored, and managed in accordance with institutional policies and applicable privacy regulations. Identifiable data (including name, medical record number, and contact information) will be stored separately from study datasets in a secure, password-protected digital repository accessible only to authorized study personnel. Research data used for analysis will be de-identified and assigned a unique study code. No identifiable information will be shared externally, included in publications, or transferred outside the institution. During follow-up and data entry, paper documents will be kept in locked research cabinets within restricted-access areas. After study completion, de-identified datasets will be retained for the period required by institutional guidelines, while identifiable information will be destroyed to ensure long-term confidentiality.

## 3. Discussion

### 3.1. Rationale and Innovation

This trial represents the first randomized evaluation of repurposing a physiological diagnostic tool as a behavioral “nudge”. While the prognostic utility of CPET is well-documented, this protocol innovates by leveraging the anticipation of the test itself to drive patient engagement. This protocol innovates by integrating clinical diagnostics with health psychology theories. By framing CPET as a “teachable moment” and a “cue to action”, we aim to transform the diagnostic process itself into a motivational lever. If effective, this strategy addresses the critical implementation gap in cardiac rehabilitation without requiring expensive digital infrastructure or labor-intensive case management.

### 3.2. Strength and Limitation

This study has several strengths. First, the randomized design minimizes selection bias, providing high-quality evidence regarding the causal effect of the announcement strategy. Furthermore, the intervention is low-cost and highly scalable, utilizing existing hospital resources rather than external funding or technology. At last, the inclusion of a determinant analysis allows for understanding of “who” responds to this incentive, aiding in the future personalization of care.

However, limitations are anticipated. As a single-center study, the generalizability of findings to rural hospitals or different healthcare systems may be limited. Additionally, due to the nature of the behavioral intervention, blinding of participants is not possible, which may introduce performance bias. Finally, the primary endpoint focuses solely on initial attendance; consequently, the study design does not enable the assessment of long-term adherence or hard clinical outcomes, such as re-hospitalization or mortality, despite existing evidence demonstrating favorable long-term outcomes with sustained participation in cardiac rehabilitation [21].

### 3.3. Clinical Implication

The results of this trial could have immediate implications for clinical practice. If the hypothesis is confirmed, incorporating a “CPET announcement” into standard discharge pathways could become a routine, evidence-based strategy to boost rehabilitation engagement. Conversely, if the intervention proves ineffective, the determinant analysis will still provide valuable data on the barriers facing Taiwanese ACS patients, guiding the development of alternative strategies.

## 4. Conclusions

Improving participation in cardiac rehabilitation is a global public health priority. This protocol describes a novel, theory-driven approach to bridge the gap between acute care and outpatient rehabilitation. By evaluating whether a scheduled clinical test can act as a behavioral nudge, this study seeks to provide a practical solution to enhance the continuum of care for ACS survivors.

## Figures and Tables

**Figure 1 jcm-15-00319-f001:**
[figure not shown]
Study scheme.

## Data Availability

Data sharing is not applicable to this article as no datasets were generated or analyzed during the current study protocol phase. The final dataset will be available from the corresponding author on reasonable request upon completion of the trial.
